## Abstract

**Background:**

Fluctuations in daily stress and the inability to cope with this stress (i.e., coping) can negatively impact behavior and potentially weight loss. Longitudinal studies using ecological momentary assessment (EMA) of psychological factors and behavior may inform interventions that can be adapted in real-time to modify stress and stress-related factors to enhance weight loss. This study’s purpose is to examine variability in stress and stress-related concepts and weight loss during a behavioral weight loss program with the intent of this informing future interventions.

**Methods:**

Individuals with obesity (body mass index: ≥ 30 kg/m^2^) who are newly enrolled in an existing community-based behavioral weight loss programs will be recruited. Participants will complete four visits, to coincide with before program (week-0), early program (6-weeks), program mid-point (3-months), and program end (6-months). Each visit will include height, weight, and questionnaires related to chronic stress and coping, and weight-related behaviors. Participants will then complete at least 14-days of EMA, including one morning survey, four signal-contingent surveys during fixed 3-hour windows, and one night-time survey daily via a smartphone application. During these 14-days, participants will also complete device-based measures for physical activity and sleep and waking saliva collection to evaluate cortisol. The primary exposure is the difference (i.e., variability) in signal-contingent survey stress, coping, and affect at baseline. The primary outcome is weight change across 6-months. This study received initial startup in March 2024, and was registered in Clinical Trials in October 2024. The study began recruitment in March 2025 and anticipate completion in early 2027.

**Discussion:**

Findings may inform justification for the pursuit of an ecological momentary intervention focused on improving stress while engaging in a behavioral weight loss intervention to support behavior change and potentially weight loss.

**Trial registration:**

ClinicalTrials.gov NCT06668259

## Introduction

By 2030, over 50% of adults will have obesity based on current population-based trends [1]. Obesity prevalence can be reduced by individual-focused lifestyle interventions as these programs are generally effective at helping people lose weight [2,3]. However, some people who engage in these interventions lose less weight than others [4]. This difference in weight loss may be influenced by psychological factors, such as perceived stress, that play a key role in behavior change [4]. Intensive longitudinal assessment of these psychological factors and daily behavior can inform the design of adaptive interventions that can intervene in real-time to change stress and thereby behavior, improving weight loss success.

Fluctuations in daily stress and inability to cope with stress (i.e., coping) can negatively impact behavior, thus weight loss [5]. However, successfully assessing this relationship on the day-to-day level has been difficult. Ecological momentary assessment (EMA) methodology can address this limitation by assessing the antecedent (*what happened before the behavior*), the behavior, and the consequence (*what happened after the behavior*) pathway, thus evaluating the temporality of state and behavior. Accordingly, EMA methodology includes sending short surveys [6], via mobile application on phone (mHealth), on psychological measures and behavior context. Studies using EMA methodology found that momentary stress and related health constructs (e.g., affect) are correlated with cortisol levels [7] and other health parameters (e.g., blood pressure) [8]. These findings were demonstrated in an EMA study amongst 143 children (ages 8–12 years), where morning self-reported stress was negatively associated with same day moderate-to-vigorous physical activity (MVPA), but not salivary cortisol collected after wakening [9]. In addition to stress, a person’s affect (i.e., emotion and mood) may also impact their ability to be active thus lose weight. In a systematic review of EMA studies (*n* = 12), positive affect predicted subsequent physical activity, but not negative affect [10]. Therefore, one’s higher perceived stress, lower coping, and lower positive affect may hinder physical activity [10], lead to poor eating behaviors [11], and limit weight loss.

Investigating daily psychological factors and obesity-related behaviors using EMA across a weight loss intervention may inform creation of an adaptive intervention. Data collected from EMA methodologies can lead to adaptive mHealth interventions, including ecological momentary interventions (EMI) which provide in-the-moment support based on self-report or device feedback to prevent behavior relapse [12]. One possible option where EMA may be used to promote behavior change is physical activity. Engaging in physical activity can be used to cope with stress, suggesting an EMI could propose physical activity amongst low coping times, and promote weight loss [13]. Investigating these claims while an individual is undergoing behavior change (i.e., weight loss) may help identify if these behaviors are valuable focus points for future adaptive weight loss interventions.

### Objective and aims

The overarching aim of this study is to elucidate potential pathways of stress and stress-related concepts with subsequent health behaviors during a behavioral weight loss intervention. The primary exposure is the difference (i.e., variability) in signal-contingent survey stress, coping, and affect early in the program. The primary outcome is weight change across a behavioral weight loss program, and secondary outcomes are physical activity and sleep. We hypothesize that high variability in daily stress will be related to less weight loss across the initial (12-weeks) and full (26-weeks) program (Hypothesis 1a). Our second hypothesis is that high variability in daily stress will be related to less physical activity and sleep across the initial and full program (Hypothesis 1b). These hypotheses were constructed as higher variability and fluctuations aligns with past literature that with individuals who experience lower stressful daily events and who are able to cope consistently and easily with this daily stress may be more active and lose more weight compared to individuals experience daily changes in stress and are less able to cope or find it difficult to do so [5,14]. Finally, we hypothesize that high variability in coping and positive affect will be related to less weight lost across the initial and full program (Hypothesis 2).

## Methods

### Study design

The current study, intensive longitudinal assessment of stress and stress-related behaviors across a behavioral intervention or *INSTANT*, is a prospective observational cohort of individuals enrolled in a community-based weight loss program. The University of Kansas Medical Center Institutional Review Board (IRB) approved this study in May 2024 (IRB#:00160436) and registered with ClinicalTrials.gov in October 2024 (NCT06668259). The current protocol follows the reporting guidelines for EMA studies (See S1 Table). This study was approved by the local IRB prior to study implementation, and in compliance with US Federal Regulations and local IRB policies, this study undergoes annual IRB review with an extension provided on at least an annual basis.

### Participants, eligibility, and recruitment

This study seeks 50 individuals who are newly enrolled in a community-based weight loss program centered in a metropolitan area of a Midwest state. Participants will be recruited from an existing 6-month-long community-based weight management program hosted by the University of Kansas Medical Center, local Diabetes Prevention Programs and other behavioral weight loss programs in the local area that may range from 6 to 12-months long. These weight management programs typically include trained health educators, 1-hour weekly video meetings, group peer support, structured nutrition plan (low calorie diet), personalized activity recommendations, and behavior change modifications [15]. Prospective participants will be recruited at their initial consultation or orientation visit for their behavioral weight loss program. Flyers will also be presented to participants at their initial visit. Measures were planned to coincide with initial enrollment (week-0), early weight change (week-6), and later weight change measures (week-12, week-26).

To be included, participants must be newly enrolled or plan to enroll in a community-based weight management program, must be over 18 years of age, have body mass index (BMI) ≥30 m/kg^2^, own a smartphone and be willing to download the mobile application to receive text messages [16]. Participants who chose to cease their community-based weight management program involvement after enrolling in the INSTANT study can still participate in later assessments, improving upon past studies which only included individuals who completed their program [17,18]. Indeed, stress may impact continued engagement in a weight management program. Participants will be excluded for being currently prescribed FDA-approved medications for weight loss, treatment for a medical condition that could affect body weight, or impacting stress levels (e.g., antidepressants), a current psychological condition that is untreated, hospitalization for a psychological condition within the past 12-months, or not being on a stable dose of treatment for at least 6-months. Other exclusion criteria are not being fluent in writing or speaking the English language, mobility limitations so they are unable to perform physical activity, and a family member who was previously enrolled or is currently enrolled in the study.

### Procedures

#### Screening.

Interested participants will complete a web screening tool using a secure online platform [19]. If a participant qualifies but is not currently enrolled in a community-based weight loss program, staff will provide them with local options so they are able to enroll and meet inclusion criteria. Potential participants who met screening criteria will be contacted for an initial phone call, during which a trained staff member will inquire about the participant’s ability to travel to visits, wear an accelerometer on their wrist, complete a salivary cortisol kit and EMA surveys related to stress and sleep patterns as well provide their health history and current medication usage. Eligible individuals will be scheduled for their baseline visit (week-0).

#### Baseline (week-0).

In the first visit, written consent will be obtained from the participant prior to performing study procedures. Height and weight will be assessed by a trained staff member. The participant will complete questionnaires and will be fitted with an accelerometer to wear for 14-days. Participants will also be provided a 5-day salivary cortisol kits. The procedures for collecting, storing and transporting the saliva samples will be explained by trained staff in additional to the participant watching a short tutorial on the collection process and provided with written instruction. Participants will have the EMA app downloaded to their phone, and receive a tutorial on the app. Beginning the next day after the baseline visits, the participant will respond to EMA prompts for 14-consecutive days and wear the accelerometer. After 14-days, participants will return their accelerometer and saliva kit and delete the EMA app off their phone.

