#### Primary outcome: Weight.

Participants’ height (cm) and weight (kg) will be objectively measured by a trained research assistant using standard operating procedures, such as shoes removed, with a mounted stadiometer and portable scale. Measurements will be taken in duplicate and an average was used. If the measurements differed by more than 0.5 units, then a third measurement was taken. Body mass index (BMI, weight/height^2^, kg/m^2^) will be calculated. Weight at Visits 2−4 will be subtracted from Visit 1 (Week-0) to calculate change in weight.

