### Analytical approach

#### Aim 1: Examine the association between variability in individual stress and weight change.

For hypothesis 1a, that high variability in daily stress will be related to less weight loss, linear regression will examine week-0 average and change frequency in daily stress (morning survey) with weight change at week-12 (visit 3) and week-26 (visit 4). For hypothesis 1b, that high variability in daily stress will be related to less physical activity and sleep, multi-level models with logit link function (and binomial distribution) will be used to examine association between week-0 morning stress and same day MVPA and sleep, with an interaction of time/day*morning stress. For exploratory analyses, we will examine the associations of daily stress with MVPA and sleep at other time points (week-6, week-12, and week-26), lagged day effects of stress (i.e., stress on day 1 influencing MVPA and sleep on day 2) to preserve temporal ordering and considering inverse probability weighted marginal structural models, and the outcome of weight change at week-6.

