#### Aim 2: Examine the association between variability in coping and positive affect and weight change.

To address hypothesis 2, that high variability in coping and positive affect will be related to less weight loss, linear regression will examine week-0 average and change frequency in coping (morning survey) and positive affect (within day survey) with weight change at week-12 and week-26.

Potential covariates for both models include number of ACEs, program compliance (i.e., number of sessions attended), coping mechanisms (number and type), age, and sex. Statistical significance will be set at *p* = 0.05. All available data will be analyzed with a sensitivity analysis for individuals with complete data. Significant weight loss will be seen at 12-weeks (12.7 ± 19.9 kg), and 6-months (12.7 ± 35.2 kg) based on past studies in our community-based weight loss program allowing us to compare weight loss in Hypothesis 1a and 2. [15]

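### The week-0 exposure is collected over days 1–14, inside the interval in which weight change accrues, and the H1a and H2 regressions cannot separate early weight change acting on variability from the hypothesized direction

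*Protocol article*

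**What the plan says.** At the baseline visit, "Height and weight will be assessed by a trained staff member" (Procedures, Baseline). The exposure data follow: "Beginning the next day after the baseline visits, the participant will respond to EMA prompts for 14-consecutive days and wear the accelerometer". Under Primary outcome: Weight, the weight at Visits 2–4 "will be subtracted from Visit 1 (Week-0) to calculate change in weight", so a positive value is a loss and every interval starts on day 0. Weights are scheduled at weeks 0, 6, 12 and 26 (Participants, eligibility, and recruitment), with none at day 14.

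For Hypothesis 1a, "linear regression will examine week-0 average and change frequency in daily stress (morning survey) with weight change at week-12" and at week 26. Hypothesis 2 has the same design for coping and positive affect. On adjustment: "Potential covariates for both models include number of ACEs, program compliance (i.e., number of sessions attended), coping mechanisms (number and type), age, and sex". Early weight change is not among these.

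The analytical approach raises temporal order once, among the exploratory analyses of Aim 1: "lagged day effects of stress (i.e., stress on day 1 influencing MVPA and sleep on day 2) to preserve temporal ordering", with marginal structural models under consideration. The outcomes named there are MVPA and sleep. The exploratory week-6 weight outcome is also counted from Visit 1.

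The abstract places the exposure at baseline, whereas the objectives place it early in the program.

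**The concern.** A baseline exposure normally precedes the outcome. Here the ratings that form it are gathered while the first two weeks of the outcome are accruing. A participant who loses weight readily at the start may report steadier stress, coping or mood because of that loss. This would produce more variability alongside less loss, which is the hypothesized pattern. If early loss also predicts later loss, the association extends to the whole interval.

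The protocol makes such an influence plausible without showing that it occurs. The programs typically include a low-calorie diet and weekly meetings, and the Discussion accepts that use of coping mechanisms may improve as people engage with a program.

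The findings are meant to help justify a momentary intervention on stress. That use depends on the direction of the association, which the planned weight regressions cannot establish.

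**Working it through.** **1. Overlap, from the protocol alone.** Visit 1 weight is day 0 and the exposure window is days 1–14. The share of each outcome interval is 14 divided by its length in days:

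| Weight outcome | Interval (days) | Overlap |
|---|---|---|
| Week 12 | 12 × 7 = 84 | 14/84 = 16.7% |
| Week 26 | 26 × 7 = 182 | 14/182 = 7.7% |
| Week 6 (exploratory) | 6 × 7 = 42 | 14/42 = 33.3% |

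The week-6 outcome has the largest overlap, so it does not act as a check.

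**2. What the overlap could do, on assumed inputs.** The protocol gives none of the following:
- SD of loss in days 1–14: s1 = 1.5 kg
- SD of later loss: s2 = 4 kg
- correlation of variability with early loss: b = −0.2 to −0.4
- correlation of early with later loss: ρ = 0 to 0.4
- participants analyzed: 45 (the plan seeks 50)

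Variability is given no effect on weight. The induced correlation with total loss is

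r = b(s1 + ρ·s2) / √(s1² + s2² + 2ρ·s1·s2)

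- Low end (b = −0.2, ρ = 0): −0.2 × 1.5 / √(2.25 + 16) = −0.30/4.27 = −0.07.
- High end (b = −0.4, ρ = 0.4): −0.4 × (1.5 + 1.6) / √(2.25 + 16 + 4.8) = −1.24/4.80 = −0.26.

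Simulated two-sided 5% tests reject in about 8% to 41% of studies over this range.

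**3. How far the size depends on the assumptions.** A second grid used n = 50, spread of loss proportional to time, b = −0.3 or −0.5, and ρ from 0 to 0.9.

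| Outcome | Induced correlation | Rejection rate |
|---|---|---|
| Week 12 | −0.06 to −0.46 | 7% to 93% |
| Week 26 | −0.03 to −0.45 | about 5.5% to 93% |

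The low ends apply when early and later loss are uncorrelated, the high ends when they correlate 0.9. So the problem is slight if early loss does not predict later loss and can be large if it does.

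**4. What a week-6 landmark achieves.** Later loss was split at week 6 in proportion to time. The share after week 6 is (12 − 6)/(12 − 2) = 60% for week 12 and (26 − 6)/(26 − 2) = 83% for week 26. On the inputs of step 2:

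| Analysis | False positive rate |
|---|---|
| Change from Visit 1 (as planned) | about 8–41% |
| Change from week 6 | about 4–16% |
| Change from week 6, adjusted for week 0–6 change | about 5–8% |

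The 4% is the nominal 5% within simulation error. The landmark alone leaves bias when early and later loss correlate: counting all loss after day 14 still gives r = b·ρ = −0.4 × 0.4 = −0.16 at the high end. Adjustment removes most of it. A little remains because week 0–6 change is an imperfect stand-in for the unmeasured change over days 0–14.

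**5. Agreement in direction is too weak a check.** Of the spurious significant results in step 2, about 94–100% kept their direction from week 6 onward. The intervals share most of their variance, so a rule asking only for the same sign would reject almost nothing.

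**The case against.** Four arguments carry weight.

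- **Sensitivity analyses often sit in the statistical analysis plan, which is not shown.** True, and their absence from a journal article is not in itself a fault. The point rests on what the article does fix: the exposure window, the origin of weight change, and regressions of one on the other.
- **The study is observational and its hypotheses are associational.** This stands. The regressions are a valid description of association. The difficulty arises when the result is read as variability coming before poorer weight loss.
- **Early loss may be small.** The abstract puts Visit 1 before the program, and some entrants only plan to enroll. Program start is not fixed relative to the first EMA day, so for some participants the window may precede any program-driven loss. The overlap with the measured outcome remains, because change is counted from day 0.
- **The illustration is entirely assumed.** It also omits the week-0 average, which the plan names beside change frequency. If the two enter one model, the average might absorb part of a general lift in mood.

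A reader might infer that reverse influence is present, that the false positive rate will be near 41%, or that the primary analysis is invalid. The documents support none of these. They establish the overlap and the lack of a stated weight analysis that addresses it, and they give no correlation from which to size the effect.

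**Conclusion.** The concern holds in a limited form. The exposure window coincides with 16.7% of the week-12 interval and 7.7% of the week-26 interval. No weight analysis in the article separates early weight change acting on variability from the hypothesized direction. The only stated attention to temporal order is exploratory and concerns MVPA and sleep.

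Whether this biases the result, and by how much, is unknown. It requires both that early loss affects reported variability and, for a material effect, that early loss predicts later loss. It may be small, more so at week 26 and for participants whose 14 days precede program start. A safeguard is worth adding because any such bias can favor the hypothesis and the week-6 weight is already scheduled.

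**What to change.** - Add a pre-specified sensitivity analysis to H1a and H2. Regress weight change from week 6 to week 12, and from week 6 to week 26, on the week-0 exposure, adjusted for week 0–6 weight change.
- Compare its estimates and confidence intervals with those of the main analysis. Do not rely on agreement in direction alone.
- Describe the exposure consistently as measured early in the program, replacing the baseline label in the abstract.
- Limit any statement that variability precedes poorer weight loss to what the landmark estimate supports.

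The cost is two further regressions per exposure on data already planned, with no added participant burden. Nine participants had been enrolled by January 2026, so it can still be specified before the outcome data are complete. The landmark estimate is less precise, needs a week-6 weight, and removes any true effect acting through weeks 0–6. It therefore supplements the main analysis and does not replace it.

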#### Follow-up visits (week-6, week-12, week-26).

At Visit 2–4, participants will have their height and weight measured, complete questionnaires, be provided the 5-day salivary cortisol collection kit, have an accelerometer fitted to their wrist to wear for 14 days and have the EMA app reinstalled on their phone to conduct the same EMA questions for 14-days. To reduce questionnaire burden in follow up visits, participants were given the option to complete questionnaires 1-week ahead of the visit using an online tool (REDCap). Harms and adverse events will be assessed at each visit. Study assessments are low-risk, thus we anticipate few study-related harms.

### Measures

As shown in Fig 1, momentary stress, demographics, attendance, stress and related concepts, health behaviors, and weight will be collected across this study.

**Fig 1 pone.0357572.g001:**
[figure not shown]
Schedule of enrollment, and assessments during study.

